### Allocation and blinding

After being assessed for eligibility, patients are randomly allocated to either the intervention or control group (allocation ratio 2:1). The larger sample size in the experimental group allows more variables to be tested and gives more power to detect relevant effects in the experimental intervention. Randomization is realized via an adaptive stratified sampling (i.e., minimization) through the computerized encrypted cloud-based database (electronic case report form (eCRF)), which takes into account three conditions to balance the two groups: (1) time since stroke (≥ 30 days), (2) age (≥ 20 years old), and (3) severity (≥ 2 MRC). The allocation is concealed while patients and clinicians (except those involved in the baseline assessment) are not blind to the group allocation. A sham group was excluded from the design because an earlier study has shown a superior rehabilitation effect of training with RGS over sham computer game training using the Wii gaming console [10]. Since this is a first-of-a-kind study evaluating the outcomes (see Tables 2 and 3.) of an AI platform for rehabilitation, the sample size has been determined by feasibility (3 years) and estimated by considering the monthly number of eligible inpatients and outpatients of the participating hospitals. We plan to include a total of 90 patients via the clinical partners in the consortium. Each hospital will be recruiting 30 patients, 20 in the intervention group and 10 in the control group.

**Table 2 Tab2:** Study procedure and assessment

Study procedure	Screening and baseline assessment		Control group, standard care	Intervention group, 0–3 months daily sessions of 24 min or more	Post-treatment assessment		
	Inpatients	Outpatients			3 months	6 months	12 months
Informed consent	x	x					
Medical history	Patients’ demographics MRI/CT scan when available						
Assessment: domains and scales							
Disability and impairment	Barthel Index (BI)				x	x	x
	Stroke Impact Scale (SIS)				x		x
	Fugl-Meyer Assessment of the upper limb (UE-FM)				x	x	x
	Chedoke Arm and Hand Activity Inventory (CAHAI)				x		x
	Hamilton Depression Rating Scale (HDRS)				x		x
	Visual analog score (VAS) for pain				x		x^a^
	Modified Ashworth Scale (AS) for spasticity				x^a^		x
	Fatigue Severity Scale (FSS)				x		x
	Grip force^a^				x^a^		x^a^
	Kinematics from the motion capture camera of the RGS@home system				x	x	x
	RGSwear data (paretic arm)				Continuous		
	Incidents related to use				x		x

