## Statistical method

We will perform mainly between-subject analysis by comparing the mean outcomes of the experimental group with the mean outcomes of the control group. To analyze the clinical outcomes related to disability and impairment, we will calculate the normalized improvement, which shows improvement or decline in proportion to the maximum score possible in the respective scale, therefore avoiding ceiling effects. Depending on whether the data is following a normal distribution, we will use parametric or non-parametric statistics. In the case of non-normal data, medians will be reported. We will perform an intention-to-treat analysis. The last observation carried forward analysis will be performed alongside a complete-case analysis to account for missing data.

To address the *primary outcome on disability and impairment*, a between-subject analysis will be used to compare the change in disability (Barthel Index (BI)) between the experimental and control groups at baselines 3, 6, and 12 months.

For the *secondary outcomes* on usability and impairment and other planned comparisons, we will perform the following analysis (for abbreviations, see Table 2):

Changes in independence (CAHAI), participation (SIS), depression (HDRS) fatigue (FSS), pain (VAS), spasticity (mAS), and impairment (BI and FM-UE) are analyzed from baseline to months 3 and 12.

We will also look at the change in grip force and correlate it with FM-UE, CAHAI, and BI from baseline to 3 months and 12 months. The outcomes of this measure are important to evaluate the clinical effectiveness of the RGS intervention to reduce disability and impairment. To measure quality of life, we compare the group changes in the quality of life (SSQOL) and well-being (SF-36) from baseline to 3 months and 12 months. We will also compare well-being (SF-36) at 6 months.

For the additional variables shown in Table 3, we will proceed as follows:

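### The Barthel Index and the other scales are compared between arms as change from baseline with no baseline covariate named: a valid comparison, but less precise than a baseline-adjusted one

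*Protocol article*

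**What the plan says.** The Statistical method section opens with the general approach: "We will perform mainly between-subject analysis by comparing the mean outcomes of the experimental group with the mean outcomes of the control group". Disability and impairment scales are first transformed: "we will calculate the normalized improvement, which shows improvement or decline in proportion to the maximum score possible in the respective scale". The test follows from the distribution: "Depending on whether the data is following a normal distribution, we will use parametric or non-parametric statistics".

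For the disability component of the primary outcome, "a between-subject analysis will be used to compare the change in disability (Barthel Index (BI)) between the experimental and control groups". The secondary list (CAHAI, SIS, HDRS, FSS, VAS, mAS and others) is also framed as changes and ends with "impairment (BI and FM-UE) are analyzed from baseline to months 3 and 12". The SSQOL and SF-36 are handled likewise: "we compare the group changes in the quality of life (SSQOL) and well-being (SF-36) from baseline to 3 months and 12 months".

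The only covariates named for a treatment comparison are cerebrovascular risk markers, in the readmission paragraph of the same section. The regression at the end of that section predicts clinical change from kinematics; it does not compare arms. Under Allocation and blinding, the minimisation "takes into account three conditions to balance the two groups": time since stroke, age and MRC severity. Baseline BI is not among them.

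**The concern.** A change score fixes the coefficient of the baseline at 1. If the regression slope of follow-up on baseline is below 1, change is negatively related to baseline: patients who start low tend to gain more and patients who start high tend to gain less, in either arm. On a scale with a ceiling, such as the BI, compression at the top pushes the slope further down.

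Two things follow. The comparison carries variance that the baseline score could remove. And if the RGS arm happens to start lower, the observed difference in change leans towards RGS; if it starts higher, it leans against. Sample size here was set by feasibility, so precision cannot readily be bought with more patients, and the baseline score is the cheapest source of it.

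**Working it through.** **Inputs from the article.** Three hospitals each recruit 20 intervention and 10 control patients: 3 × (20 + 10) = 90, which reproduces the stated total, split 60:30. No SD, mean, expected gain, correlation, alpha or power is given. Everything below that uses such a figure is an assumption, shown over a range.

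**Does the normalisation adjust for baseline?** As worded, change is divided by the scale maximum, which is the same constant for every patient, so it cancels from any test statistic. In a simulation with no treatment effect (assumed BI baseline mean 60, SD 20), the correlation between the estimated effect and the chance baseline difference was −0.56 at rho = 0.5 and −0.46 at rho = 0.7. It was identical for raw and rescaled change, and about 0 for the baseline-adjusted estimate. Even if the normalisation meant change divided by the room left to improve, which is not what the text says, −0.30 and −0.08 would remain.

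**Closed form, equal SDs, baseline-to-follow-up correlation rho.** Variance of change is proportional to 2(1 − rho). Variance with baseline as covariate is proportional to 1 − rho² = (1 − rho)(1 + rho). The ratio, adjusted to change, is (1 + rho)/2.

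- rho 0.5: ratio 0.75, a 25% reduction; 90 patients analysed by change are worth 90 × 0.75 = 67.5 analysed with adjustment.
- rho 0.7: ratio 0.85, a 15% reduction; worth 76.5.
- rho 0.9: ratio 0.95, a 5% reduction; worth 85.5.

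For an illustrative effect of 0.5 SD (60:30, two-sided alpha 0.05), power for change versus adjusted is 61% versus 73% at rho 0.5, 82% versus 88% at 0.7, and over 99% for both at 0.9.

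**Chance imbalance.** The standard error of the baseline difference is √(1/60 + 1/30) = 0.224 SD, so its 95% range is ±1.96 × 0.224 = ±0.44 SD. The change-score estimate moves by −(1 − rho) × difference. For a 0.44 SD difference that is 0.22 SD at rho 0.5, 0.13 SD at 0.7 and 0.04 SD at 0.9. Under a linear model the adjusted estimate does not move.

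**Simulation of a capped BI.** Assumptions: 60:30, 5-point steps limited to 0–100, baseline mean 60 and SD 25 before capping, latent effect 10 points, Welch test on change versus ANCOVA, 4,000 replicates per setting. Mean gain and rho were varied:

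| Mean gain | rho | Variance reduction | Power, change | Power, adjusted |
|---|---|---|---|---|
| 20 | 0.5 | 40% | 29% | 48% |
| 20 | 0.6 | 35% | 34% | 52% |
| 20 | 0.8 | 31% | 54% | 72% |
| 10 | 0.8 | 16% | 68% | 78% |
| 10 | 0.9 | 12% | 91% | 95% |
| 5 | 0.8 | 12% | 73% | 81% |
| 5 | 0.9 | 9% | 93% | 96% |

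Over all settings and repeat runs the reduction is about 8% to 41% (about 8% to 33% when the gain is 5 to 10 points), and power rises by about 2 to 19 percentage points. Type I error is about 5% for both methods.

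Capping brings the baseline SD to about 23.5, so one SD of the chance baseline difference is about 0.224 × 23.5 ≈ 5.3 points. The slope of the change-score estimate on that difference runs from −0.33 to −0.63 at a 20-point gain, hence a shift of about 2 to 3 points. With smaller gains and higher rho the shift falls to about 0.7 points.

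**The case against.** The strongest reply is that the article is silent here and has not chosen against adjustment. It names no specific test or model, and it qualifies its general approach with the word mainly. Change can itself be the response in a model that contains the baseline; the arm effect is then identical to ANCOVA on the follow-up score. A statistical analysis plan, not shown here, could add the covariate. A reader might infer that the trial will definitely be analysed unadjusted, and the article does not establish that. What remains is that the analysis as stated compares mean changes with parametric or non-parametric tests, and that it names covariates for readmission but none for the scales. A plan that adjusted would go beyond the published method.

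A reader might also infer that the treatment effect will be biased or the test invalid. That does not follow. Over repeated randomisations the change-score estimate is unbiased, and its standard error already covers chance imbalance. The error is conditional on the imbalance that happens to occur.

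Third, a gain of 30% to 41% might be taken as typical. It rests on an assumed 20-point mean improvement, which pushes many patients to the cap. The trial includes chronic as well as subacute patients, so smaller gains and higher correlations are possible, and the benefit is then modest.

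Two further limits stand. Minimising on MRC severity may balance BI indirectly. And only the BI under a Welch test was quantified: BI is one of five domains in the compound primary outcome, and the rank-test branch and the other scales were not simulated.

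**Conclusion.** The point holds as a matter of efficiency. The stated comparison is valid, but for any correlation below 1 (equal SDs) it is less precise than the same data allow, apart from the one degree of freedom that the covariate costs. It also leaves the estimate exposed to chance baseline differences on a variable that is not a minimisation factor.

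The loss is small if correlation is near 0.9 and gains are small, and material if correlation is nearer 0.5 or many patients approach the ceiling. The article gives nothing to place the trial within that range. For the other scales only the direction carries over, by the same algebra; the size is not established.

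**What to change.** State in the analysis plan, before any comparison by arm, that each scale is analysed with the follow-up score as response and with arm and that scale's own baseline score as covariates. This can be ANCOVA at each time point or a repeated-measures model with baseline as covariate. Name it as the main analysis for BI. Where residuals are clearly non-normal, keep the baseline covariate and use robust or bootstrap intervals, or an ordinal or rank-based model that includes baseline, in place of an unadjusted two-sample test. Show raw and normalised change descriptively.

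If the plan already does this, one sentence in the published method would settle the matter. The clinical scales are already collected at baseline, so the cost is wording and one degree of freedom per model, with no new patients or data.

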	Number and reason of dropouts				x		x
	Acceptability and usability Questionnaire for patients and physicians.				x	x	x
Quality of life	Stroke Specific Quality of Life scale (SSSQOL)				x		x
	Number of falls				x	x	x
	Short-Form-36 (SF-36)				x	x	x

^a^Included in the eCRF but not in the trial registry

**Table 3 Tab3:** Additional variables collected via eCRF

Assessment		3 months	6 months	12 months
Readmission	Number of outpatients that return to the hospital after discharge	x	x	x
	Reason for readmission	x	x	x
	Days of hospitalization due to readmission	x	x	x
	Costs of readmission	x	x	x
	Presence of CVA risk markers such as waist to hip ratio, smoking cessation, blood pressure, hypertension, and blood markers	x	x	x
Cost of treatment	Total cost of therapy	x		x
	Hours of therapy	x		x
	Total cost of traveling from home to hospital	x		x
	Hours of traveling from home to hospital	x		x
	Number of days of inpatient hospitalization	x		x
Quality of life	Return to work	x	x	x
	Number of formal caregiver hours per week	x	x	x
Acceptability	Number of hours of system use at home	x		x
	Number of hours technical/visits to patients’ home	x	x	x
	Number of equipment replacements	x		x
	Incidents related to use	x		x

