#### Primary outcome measures

One main outcome measure is calculated as a compound score summarizing the main outcome of each of the 5 domains: (1) disability and impairment (Barthel Index for independence in activities of daily living), (2) readmission (number of patients who return to the hospital (inpatient) after being discharged to at-home status), (3) cost of treatment (total cost of the therapy), (4) quality of life (the Stroke Specific Quality of Life Scale), and (5) acceptability (amount of use at home).

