*Readmission*: We compare between the groups the number of outpatients that return to the hospital after discharge to at-home status, including readmission due to complications unrelated to stroke, from baseline to 3, 6, and 12 months. We also compare the days of hospitalization and their associated costs. Here, we will take into account the presence of CVA risk markers as covarying variables. The readmission outcome is used to evaluate the effectiveness of the RGS intervention in reducing, or at least not increasing, a hospital’s readmission after discharge compared to standard care.

*Cost of treatment*: We compare the total cost of rehabilitation therapy/hour provided at the hospital or in the community and transportation costs/hour between the hospital and home at 3 months and after 12 months. We also compare days/hours of hospitalization and whether additional therapy, not replacing the RGS-based training (e.g., magnetotherapy, electrotherapy, thermotherapy), was provided. These outcomes allow us to evaluate the RGS’s effectiveness to reduce the cost of treatment.

*Quality of life*: We will compare between the groups the number of falls reported at 3 months and 12 months. In addition, we will compare how many patients were able to return to work and how many hours professional care was provided at 3 and 12 months. These outcomes facilitate the evaluation of the impact of the RGS ecosystem on quality of life and evaluate any risks arising from using the RGS system at home.

*Acceptance*: We will assess the RGS@home use (hours) after 3 months, 6 months, and 12 months. In both groups, we will keep track of the dropouts of the study. Specifically, in the intervention group, we will analyze the use of RGS at the hospital and home and the use of RGSwear. Concerning RGS@home, we will analyze the support needed (hours and visits to the patient’s home, replacement of materials, instructions, troubleshooting, etc.) and any incidents reported by the users. Also, we will analyze the patient’s evaluation of the System Usability Scale. The outcomes of this domain are important to evaluate the acceptance of the RGS ecosystem within the experimental group and the feasibility of the system for future use.

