## Discussion

The RGS@home trial is designed to evaluate the effectiveness, acceptance, usability, and cost-effectiveness of a science-based ICT solution for rehabilitation (RGS) that combines brain theory, cloud computing, and VR. The RGS system targets motor and cognitive recovery after stroke. RGS is an integrated platform to deliver personalized treatment supporting the full treatment continuum, suitable for all end-users, i.e., patients, carers, and clinicians. The RGS@home trial validates an e-health approach towards neurorehabilitation that accompanies patients during their journey to recovery from the clinic to their homes, with an emphasis on counteracting disability and impairment and improving quality of life. The trial targets to demonstrate the superiority of the RGS intervention when combined with standard care compared to standard care alone while being usable and well accepted.

The trial includes so far one-third of the total number of patients. While the main results of the trial will be published in 2023, intermediate observations on the use of the system suggest that the patients in the intervention group use RGS@home exceeding the prescribed daily usage. They also enjoy the gamified VR-based training and can easily follow the training prescribed by the therapists. Thus, our preliminary observations indicate that the RGS@home solution is well received by the patients. The clinicians across the three European hospitals find it easy to use for treatment prescription, patient monitoring, and data management. We foresee that providing therapy via the RGS system at the patient’s home will reduce the risk of readmission and prevent deterioration. We hypothesize that the additional therapy time at home positively influences arm use and reduces impairment (confirming a previous pilot study by [15]).

The proposed solution promises to be highly scalable; hence, many patients can be benefiting simultaneously without overhead on the health care personnel. In addition, it will be cost-effective since it comprises off-the-shelf devices that are ubiquitous in our society. The reduction of readmissions and prevention of deterioration should reduce transportation costs, therapy, and hospital stays. Most importantly, this AI-based training solution allows extending the hospital’s rehabilitation service treatment to the patient’s home, which will result in cost reduction for hospitals and families.

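### The cost comparison names no RGS equipment or support cost, although RGS is added to standard care, so as written it favours RGS and cannot support a claim of cost reduction

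*Protocol article*

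**What the plan says.** All references are to the Protocol article.

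- **Statistical method, cost of treatment.** The comparison is described as: "We compare the total cost of rehabilitation therapy/hour provided at the hospital or in the community". It continues with "transportation costs/hour between the hospital and home at 3 months and after 12 months", and then: "We also compare days/hours of hospitalization and whether additional therapy, not replacing the RGS-based training" was given. The paragraph concludes: "These outcomes allow us to evaluate the RGS’s effectiveness to reduce the cost of treatment".
- **Statistical method, acceptance.** Home support is handled here, for the intervention group: "we will analyze the support needed (hours and visits to the patient’s home, replacement of materials, instructions, troubleshooting, etc". The stated purpose is to judge acceptance in that group and feasibility for later use.
- **Table 3.** Total cost of therapy and hours of therapy are separate items under cost of treatment. Technical hours or home visits and the item "Number of equipment replacements" stand under acceptability, as quantities without a price.
- **Primary outcome measures.** The third of the five domains in the compound score is "cost of treatment (total cost of the therapy"), with no mention of hours.
- **Intervention and control groups.** RGS is added to standard care, and RGSwear is provided for up to one year.
- **Discussion.** Extending rehabilitation to the home in this way "will result in cost reduction for hospitals and families".

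**The concern.** An add-on treatment brings its own cost. It lowers the total only if what it displaces (therapy, travel, hospital days) is worth more than it costs. The cost paragraph lists the items in which displacement could appear. It omits the item that has to be set against them, and then says that the list answers the question of cost reduction.

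Lower cost is a stated hypothesis (Study rationale and hypotheses), and cost is one of the five domains of the main outcome. The Background also criticises earlier studies for not evaluating cost-effectiveness. A comparison that omits the intervention's own cost leans towards the hypothesis.

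A second problem is that the slash before the word hour leaves the compared quantity unclear. If it means a ratio, the analysis differs from the total cost named in the primary outcome.

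**Working it through.** The article states no cost, cost difference or standard deviation, so there is no figure to reproduce. The check is algebraic, with assumed values for illustration.

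**Inputs from the article**
- RGS is an add-on to standard care.
- Treatment dosage recommends 24–28 min of RGS per day, and outpatients train daily for 3 months. Taking 90 days, RGS hours are R = 24 × 90 / 60 = 36 h to 28 × 90 / 60 = 42 h.

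**Assumed, because the article gives none**
- Standard-therapy hours H = 20, 40 or 80.
- Price per therapy hour c = 50.
- RGS equipment and support cost per patient K = 500 to 3000.
- Share of standard therapy displaced by RGS, d = 0 or 25%.

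Transport and hospitalization are held equal between arms.

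**Reading 1: the slash means cost and hours, so totals are compared**
- Difference as the paragraph lists it (RGS minus control): −d × H × c
- True difference: K − d × H × c
- Error: −K per patient, whatever H, c and d are

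With H = 40 and c = 50, the control total is 2000:

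| d | K | Difference as listed | True difference |
|---|---|---|---|
| 0 | 500 | 0 | +500 (25% of 2000) |
| 0 | 1500 | 0 | +1500 (75%) |
| 0 | 3000 | 0 | +3000 (150%) |
| 25% | 500 | −500 | 0 |
| 25% | 1500 | −500 | +1000 |
| 25% | 3000 | −500 | +2500 |

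At 25% displacement, RGS saves money only if K is below 500. The listed comparison shows a saving of 500 for every K.

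**Reading 2: a ratio, RGS hours not counted**
- Control: H × c / H = c = 50
- RGS: (1 − d) × H × c / [(1 − d) × H] = c = 50

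The ratio is a unit price. It shows no difference whether RGS displaces therapy or not, and whatever K is.

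**Reading 3: a ratio, RGS hours counted, K omitted, d = 0**
- Relative change = H / (H + R) − 1
- H = 20: 20/56 − 1 = −64%; 20/62 − 1 = −68%
- H = 40: 40/76 − 1 = −47%; 40/82 − 1 = −51%
- H = 80: 80/116 − 1 = −31%; 80/122 − 1 = −34%

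Here spending on standard therapy is unchanged and the apparent saving is false. These sizes require all 36–42 h to count as hospital or community therapy, which the text does not say.

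**The case against.** **The slash probably does not mean a ratio.** A reader might infer that cost is to be analysed per hour and that RGS would show a false saving of roughly a third to two thirds. The article does not establish this. Table 3 lists cost and hours as paired separate items for both therapy and travel, the next sentence of the paragraph uses a slash between days and hours, and the primary outcome names a total. Outpatients' RGS training takes place at home, outside the hospital-or-community wording. Inpatients use RGS in hospital only until discharge, so at most part of the 36–42 h would enter such a denominator. This objection stands: the percentages under reading 3 illustrate a risk and are not a prediction.

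**The costed components may be defined elsewhere.** Total cost of therapy is not itemised for either arm, the Abstract announces a health economic analysis, and the full protocol is available on request. It would therefore go too far to say that the sponsor has decided to exclude RGS costs. But the paragraph is not merely silent. It lists what is compared, places RGS support under a different domain for a different purpose, and states the inference drawn from the list. That inference does not follow from the list.

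**Most cost items are already captured.** Hospitalization is in the cost paragraph, and readmission days and their costs are compared under readmission. This is correct. What is missing is RGS's own cost and an explicit sum per patient.

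**Conclusion.** The concern holds in this form: for an add-on treatment, the stated cost comparison names none of the intervention's own cost, yet is said to show whether the intervention reduces cost. Comparing totals as listed favours RGS by exactly the omitted cost per patient. That result needs no assumption beyond RGS having a cost that is left out. How large it is in money, and whether it would reverse the conclusion, cannot be determined from the article; the amounts in the table rest on assumed hours, prices and displacement.

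The per-hour wording is a secondary matter of clarity. As a ratio it would conflict with the primary outcome's total cost. It would then be insensitive to changes in the amount of therapy or, if RGS hours were counted, would show a false saving. Cost and hours as two separate quantities is at least as natural a reading, and it removes the ratio problem but not the omission.

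This should be corrected before the cost analysis is run.

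**What to change.** State that the comparison is mean total cost per randomised patient, from baseline to 3 months and from baseline to 12 months. Include:

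- hospital and community therapy,
- hospitalization and readmission,
- transport,
- in the RGS arm, the equipment, RGSwear, technical support hours and visits, and replacements, each at a stated unit price.

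Report the between-group difference in means with a confidence interval suited to skewed costs. A bootstrap interval is one option among several. Exempt cost from the general rule of reporting medians for non-normal data, because total spending follows from the mean. Show hours and any per-hour figure only as description, and align the wording with the total cost named under Primary outcome measures.

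The cost of the change is modest. Support hours or visits and replacements are already recorded in Table 3. The device and RGSwear have no cost item there, so unit prices for equipment and for support must be added. The downside for the sponsor is that the RGS arm's cost will look less favourable than under the present wording.

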### Adherence to treatment

It is a common problem that patients sometimes lack the motivation to follow their training program when there is no direct supervision [19]. With RGS@home and RGSwear, the patient is continuously monitored, and the clinicians can detect low adherence and contact the patients. To further improve adherence, the exercises of the RGS-based training are designed to include gamification and motivational factors to avoid monotonous training. In addition, the AI component of RGS adapts the exercises to the patient’s abilities (increases or decreases the difficulty), thus avoiding frustration or boredom and facilitating patients’ adherence. Patients are free to leave the study at any time and will not be included in the study if they stop using RGS@home for more than five consecutive days. Patients are also free to participate in leisure activities. However, they should not participate in other clinical trials investigating rehabilitation approaches or technologies.

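### The falls comparison takes no account of time observed, and the five-day non-use rule can shorten observation in the RGS arm only

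*Protocol article*

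**What the plan says.** All references are to the Protocol article.

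- **Statistical method, quality-of-life paragraph.** "We will compare between the groups the number of falls reported at 3 months and 12 months". Falls, return to work and professional care hours are together meant to inform on quality of life and to "evaluate any risks arising from using the RGS system at home". The sentence on falls names no rate, denominator or observation time.
- **Statistical method, opening paragraph.** The analysis is mainly a matter of "comparing the mean outcomes of the experimental group with the mean outcomes of the control group". Non-parametric methods and medians are used if data are not normal. The analysis is by intention to treat, with last observation carried forward (LOCF) and complete-case analyses run side by side for missing data.
- **Table 2.** Number of falls is an assessment item at 3, 6 and 12 months, listed beside the patient-level quality-of-life scales.
- **Adherence to treatment.** "Patients are free to leave the study at any time", with no limit to one arm. The same sentence adds that patients "will not be included in the study if they stop using RGS@home for more than five consecutive days".
- **Allocation and blinding.** "Each hospital will be recruiting 30 patients, 20 in the intervention group and 10 in the control group".
- **Harms.** Incidents, falls, and reasons for readmission and dropout are all collected and analysed.

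**The concern.** A fall count means something only relative to the time over which falls could be seen. Here that time can differ between arms for a reason built into the protocol: control patients have no RGS@home to stop using, so the five-day rule can end participation in the RGS arm alone. If it does, falls that occur later in those patients are not seen.

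The general rules do not repair this. They also pull against the adherence rule, since intention to treat keeps every randomised patient while the adherence rule takes some out. The error runs in the unwelcome direction for a safety comparison: lost observation lowers the RGS count and can make home use look safer than it is. Patients who stop because of a fall, or because they are becoming frailer, are also those whose later falls matter most.

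**Working it through.** **Planned numbers.** 3 hospitals × (20 + 10) = 90 patients, 60 RGS and 30 control. This reproduces the stated total. The article gives no fall rate, dropout rate or share removed under the five-day rule, so those below are assumptions.

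**1. Reading the comparison per patient.** Let RR be the true fall-rate ratio (RGS to control), and f_R and f_C the shares of planned observation time kept in each arm. If each patient is counted with the falls seen up to exit:

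apparent ratio of mean falls per randomised patient = RR × f_R / f_C

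With equal follow-up the ratio is RR, whatever the allocation. At 0.5 falls per patient in both arms, the totals are 60 × 0.5 = 30 and 30 × 0.5 = 15, but the means are 0.5 and 0.5.

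**2. Size of a hidden excess at 12 months.** Take f_C = 1. A share p of RGS patients leaves at month t, with t from 1.5 to 3, the middle to the end of the 3-month training period. Mean RGS observation is (1 − p) × 12 + p × t, and the excess that shows as equality is 12 / (mean observation) − 1.

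| p (of 60) | t | Mean observation, months | Excess hidden |
|---|---|---|---|
| 20% (12 patients) | 1.5 | 9.6 + 0.3 = 9.9 | 12/9.9 − 1 = 21% |
| 20% (12 patients) | 3 | 9.6 + 0.6 = 10.2 | 12/10.2 − 1 = 18% |
| 30% (18 patients) | 1.5 | 8.4 + 0.45 = 8.85 | 12/8.85 − 1 = 36% |
| 30% (18 patients) | 3 | 8.4 + 0.9 = 9.3 | 12/9.3 − 1 = 29% |

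At the 3-month comparison the effect is smaller. With p = 20% and t = 1.5, mean observation is 2.4 + 0.3 = 2.7 months, and 3/2.7 − 1 = 11%. With exit at month 3 it is nil.

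**3. What the two missing-data analyses do.**
- LOCF applied to a cumulative count repeats the total at the last visit, which adds zero falls after exit. This is the situation in the table. It is worse if a patient leaves before the 3-month visit and the falls up to exit are never recorded: f_R is then 0.80 at p = 20%, and 1/0.80 − 1 = 25% is hidden. The article does not say whether counts are cumulative. If they are per interval, LOCF carries a count from a 3-month interval (0–3 or 3–6) into the 6-month interval 6–12, which also does not match the time at risk.
- Complete case removes those who stopped. Its per-patient ratio is right only if stopping is unrelated to fall risk, and the table does not apply to it.

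**4. What a median shows.** For a negative binomial count with mean m and dispersion k, the share with no falls is (k/(k + m))^k.
- m = 0.5: 0.375^0.3 = 0.75 for k = 0.3; 1/1.5 = 0.67 for k = 1.
- m = 1.0: (0.3/1.3)^0.3 = 0.64 for k = 0.3; 1/2 = 0.50 for k = 1.

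So 50–75% of patients have no falls. The median is 0 throughout (at its boundary in the last case), and a doubling from 0.5 to 1.0 falls per patient leaves 0 against 0.

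**The case against.** A reader might infer that raw arm totals will be compared, so that 2:1 allocation makes equal risk look doubled. The article does not support this. It never mentions arm totals, its general rule compares means, and Table 2 lists falls among patient-level assessments. On that reading the allocation cancels, as step 1 shows. Hidden excesses of the size in step 2 also need the per-patient reading: on raw totals the 2:1 split pushes the other way.

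Nor can it be said that only the RGS arm can be cut short. Anyone may leave, and dropouts are tracked in both groups. If control patients leave as often and as early, f_R / f_C is 1 and the bias disappears. What is one-sided is the five-day rule.

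Falls are not the sole measure of risk either. The same paragraph joins them with other outcomes, and the Harms section adds incidents and reasons for readmission and dropout.

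It is also fair that a journal article commonly leaves the choice of count model to the analysis plan, and that the conflict between the five-day rule and intention to treat is not peculiar to falls. The absence of a named model is therefore no fault in itself. But the article does fix a falls comparison, a way of summarising it, two missing-data methods and a one-sided removal rule. Followed together, these do not give a sound comparison of fall risk. Finally, a rank test can still respond when both medians are 0, so the last step concerns what is reported and not whether every test fails.

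**Conclusion.** The point holds in a limited form. The falls comparison helps to judge the risk of home use but ignores time observed. The stated LOCF, complete-case and median rules do not correct for unequal follow-up, and the five-day rule can create it in the RGS arm only, against the intention-to-treat statement. Observed RGS falls can therefore be too low.

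Under complete control follow-up and exit at month 1.5 to 3, a true excess of 18–21% (20% leaving) or 29–36% (30% leaving) would appear as equality per patient at 12 months. These figures assume a constant fall rate, falls counted up to exit and the stated exit shares. The share of zero counts rests on assumed means of 0.5–1.0 and dispersion of 0.3–1.0. The documents show that the bias can arise and in which direction the one-sided rule pushes; they do not show how large it will be.

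**What to change.** - **Reconcile** the Adherence to treatment and Statistical method sections, so that every randomised patient stays in the falls analysis in the assigned arm, and falls continue to be recorded at the scheduled 3-, 6- and 12-month visits after RGS use stops. This comes first, because a rate alone corrects for lost time only when stopping is unrelated to fall risk.
- **Replace** the number of falls in the quality-of-life paragraph by falls per person-time observed. Use a negative binomial model, or Poisson with robust standard errors, with log observation time as offset, and report the rate ratio with its 95% confidence interval.
- **Report beside it** the proportion of patients with at least one fall, in place of a median count.
- **Do not apply LOCF** to the fall count.

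The cost is small. Falls are already scheduled at these visits and dropouts are already tracked, so the change is mainly one of wording. It needs dates of last observation, continued contact with patients who stop using RGS and slightly more analysis work, and it gives a wider interval that better reflects the uncertainty.
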